### Sampling strategy

For sampling purpose, the universe of study would be the entire district. For every cross-sectional survey, four blocks will be covered from the total number of administrative blocks within the district. Village/ward will be the primary sampling unit. Multi stage cluster sampling will be employed. In each selected village/ward, line list of beneficiaries (children, pregnant women, unmarried WRA (where available) and adolescents’ girls) will be collected from ASHA/ANMs/AWWs. It is recognized that the line listing will not have 100% coverage, but as a part of implementation research study, this aspect will be strengthened as interventions are rolled out. Beneficiaries will be selected randomly from the list. For the remaining groups, where ready line listing may not be available, the next 1–2 households where beneficiary was found using line listing, will be used to identify the rest of the beneficiary groups (children 5–9 years; adolescent boys; WRA & adolescent girls (incase CHWs do not have readily available list for WRA) in the stated order of priority. The sample will include a total of 50 beneficiaries from each village/ ward. The method of sampling would be the same in each of the five survey rounds.

**Sample size calculation:** It is assumed that the prevalence of anemia at baseline will be between 40–60% among different age groups as per NFHS-5 & Comprehensive National Nutrition Survey data. Assuming 20% prevalence of anemia at the end-line with 30% relative precision, 95% confidence interval, 1.45 design effect and assuming different non-response rate (40% for children 6–59 months and 5–9 years, 30% for adolescent girls and boys, 20% for women of reproductive age and 20% for pregnant women), the final sample size is calculated as 400 each for children 6–59 months and children 5–9 years, 350 each for adolescent girls and boys, 300 each for women for reproductive age group and pregnant women for each survey rounds. The focus of the study is on all the 6 groups; however, the four groups (children 6–59 months, adolescent girls (10–19 years), women of reproductive age (20–49 years), pregnant women) are selected for the evaluation of impact indicators. For the remaining two groups (children 5–9 y and adolescent boys), the focus is on the process and coverage indicators.

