**1. Impact level Indicator:**
**Primary outcome** will include prevalence of anemia among children 6–59months, adolescent girls (10–19yrs), and women of reproductive age and pregnant women (all trimesters)**Secondary outcomes** would include [1] prevalence of moderate anemia among children 6–59 months, adolescent girls (10–19 yrs), women of reproductive age and pregnant women (all trimesters); [2] prevalence of severe anemia among children 6–59 months, adolescent girls (10–19 yrs), women of reproductive age and pregnant women (all trimesters)

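### Where no ready line list exists, the household step seeks women of reproductive age (and adolescent girls) after two groups with no impact role; if one person is taken per household, the women found are a selected set.

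*Protocol article*

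**What the plan says.** The Sampling strategy section of the Protocol article describes two steps within each village or ward.

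- **Line list.** A "line list of beneficiaries (children, pregnant women, unmarried WRA (where available) and adolescents’ girls) will be collected from ASHA/ANMs/AWWs". Then: "Beneficiaries will be selected randomly from the list".
- **Household step.** This covers the groups that may have no list at hand. For them, the article says that "the next 1–2 households where beneficiary was found using line listing, will be used to identify the rest of the beneficiary groups". The order is children 5–9 years, then "adolescent boys; WRA & adolescent girls (incase CHWs do not have readily available list for WRA) in the stated order of priority".

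The take is fixed: "The sample will include a total of 50 beneficiaries from each village/ ward". No split of the 50 by group is given. Targets are set per group and survey round: 400 for each child group, 350 each for adolescent girls and boys, 300 each for WRA and pregnant women. The method is to be the same in all five rounds. The section also accepts that listing is incomplete and expects it to be strengthened during roll-out.

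On the role of the groups, the same section states: "For the remaining two groups (children 5–9 y and adolescent boys), the focus is on the process and coverage indicators". Under Outcome assessment, the primary outcome is "prevalence of anemia among children 6–59months, adolescent girls (10–19yrs), and women of reproductive age", with pregnant women as the fourth group.

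**The concern.** The order in the household step runs against the role of the groups. Two groups without an impact outcome are sought before two that carry the primary outcome.

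A priority order has an effect only when not every eligible member of a household is taken. In that case a woman is enrolled mainly where nobody ranks ahead of her, that is, in a home with no child aged 5–9 years and no adolescent boy. Such women can differ from other WRA in age and parity.

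WRA are more exposed than girls. Girls are on the line list by default. For WRA the list names only unmarried women, where available, so married non-pregnant women appear to depend on the household step.

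At stake are the WRA prevalence read against the 20% goal and its trend over five rounds. If listing improves during roll-out, the mix of listed and household-found women can shift between rounds, and a change in who is sampled could look like a change in prevalence.

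**Working it through.** **1. The plan's sample size.** With prevalence 0.20, relative precision 30% (±0.06), 95% confidence and design effect 1.45:

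- n = 1.96² × 0.20 × 0.80 / 0.06² = 170.7; × 1.45 = 247.6.
- Divided by 1 minus non-response: 247.6/0.60 = 412.6 (children), 247.6/0.70 = 353.7 (adolescents), 247.6/0.80 = 309.5 (women).

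Rounded to the nearest 50, these are the stated 400, 350 and 300. The targets themselves are not in question here.

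**2. Per-village numbers.** 2 × (400 + 350 + 300) = 2,100 per round, and 2,100/50 = 42 villages. Per village that is 400/42 = 9.5 per child group, 350/42 = 8.3 per adolescent group and 300/42 = 7.1 WRA. The check uses whole-number quotas of 10 children 5–9 years, 8 boys, 7 WRA and 8 girls.

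**3. Next households available.**

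- Girls listed (the default): index households (400 + 300 + 350)/42 = 25, so 25–50 next households.
- Girls not listed: (400 + 300)/42 = 16.7, so about 17–33.

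**4. Simulated fill.** Assumptions that are not in the article: 35% of households hold a child 5–9 years, 35% a boy, 35% a girl and 85% a WRA, independently; all WRA come from the household step; group quotas are held; at least 4,000 simulated villages per scenario. The share of all households with neither a 5–9 child nor a boy is 0.65 × 0.65 = 42%.

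Stated order, one person per household:

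| Scenario | Next households | Children 5–9 (of 10) | Boys (of 8) | WRA (of 7) | Girls (of 8) | WRA from homes with no 5–9 child or boy |
|---|---|---|---|---|---|---|
| Girls listed | 25 | 8.3 | 5.7 | 6.9 | listed | 97% |
| Girls listed | 50 | 10.0 | 8.0 | 7.0 | listed | 96% |
| Girls not listed | 17 | 6.0 | 3.9 | 5.7 | 0.5 | 100% |
| Girls not listed | 33 | 9.5 | 7.2 | 7.0 | 3.2 | 96% |

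**5. Other rules, girls listed, 25 next households.**

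| Rule | Children 5–9 | Boys | WRA | WRA from homes with no 5–9 child or boy |
|---|---|---|---|---|
| One from every open group | 8.3 | 7.4 | 7.0 | 42% |
| One person; WRA, then boys, then children 5–9 | 4.2 | 6.1 | 7.0 | 43% |
| One person; WRA, then children 5–9, then boys | 6.2 | 4.1 | 7.0 | 42% |
| One person; random among open groups present | 5.9 | 5.7 | 7.0 | 62% |

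With one person from every open group, the stated and reversed orders agree up to simulation error. With girls not listed, both give 7.0 WRA, and about 5.8 girls at 17 households and 7.9 at 33.

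**6. Sensitivity to the membership rate** (girls listed, 25–50 households, stated order, one person). At 25% membership for children and boys, 100% of WRA come from homes with neither, against 56% in the population. At 50% it is 73–77% against 25%.

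**The case against.** Four points can be made for the plan.

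- **The order is a fieldwork sequence.** Children 5–9 years and boys depend on the household step in every village; WRA and girls are a conditional fallback. That explains the order. It does not remove its effect on women once the fallback is used.
- **No shortfall is shown.** A reader might infer that WRA and girls will run short because they come last under a cap of 50. The documents do not support this. The cap equals the sum of the group targets over 42 villages, so earlier groups displace later ones only by exceeding their own targets. With girls listed, WRA reach 6.9–7.0 of 7, and at 25 households the groups that fall short are children 5–9 years and boys. The low counts of girls belong to the exception without a usable list. This part of the objection stands.
- **One person per household is not a stated rule.** The article says the households serve to identify the remaining groups, in the plural. If one person from each open group is taken, the order is harmless. This stands as a condition. Yet a stated priority order has a purpose only if some eligible members are passed over, so the text invites that reading.
- **Quotas and within-household selection may sit in a field manual.** Their absence from an article is no fault. The order, however, is fixed in the article, and quotas would protect numbers, not composition.

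Some selection also comes from the adjacent-household rule itself. It affects every group found that way and is not due to the order.

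**Conclusion.** The point holds in a limited form. Where no ready list exists, the plan seeks WRA, and in that case adolescent girls, after two groups that carry no impact outcome. If one person is taken per household, household-found WRA come almost only from homes without a 5–9 child or an adolescent boy: 96–100% against 42% at 35% membership, and still 73–77% against 25% at 50% membership with girls listed. Meeting the group quotas does not cure this. If one person from every open group is taken, the order has no effect.

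The size rests on assumed, independent household membership and on all WRA coming from the household step; any women drawn from the list dilute it. A reader might also infer that WRA prevalence will be biased in a known direction. The article gives no anemia figures by household composition, so neither direction nor size can be derived. The change is nevertheless worth making, because it is cheap and protects a primary-outcome group in all five rounds.

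**What to change.** In the Sampling strategy section, replace the fixed order with a rule such as: in each next household, enrol one eligible person from every group still open against its per-village quota. State those quotas (about 10, 8 and 7 for child, adolescent and women's groups, adjusted across the 42 villages to meet the round totals). In the check at 25 households this returned the WRA share to 42% and raised boys from 5.7 to 7.4 of 8, with children 5–9 years unchanged at 8.3 of 10.

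If only one person per household is feasible, put WRA and adolescent girls first, or choose the open group at random. Random choice among the groups present removes only part of the selection (62% against 42%), so putting WRA and girls first is the stronger option on this point.

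The cost is a change of wording, slightly more work per household and slightly more clustering within households. In the one-person case, shortfall moves to children 5–9 years and adolescent boys (with WRA first at 25 households, children 5–9 years fall from 8.3 to between 4.2 and 6.2 of 10, depending on which of the two comes next). These two groups serve process and coverage indicators only.

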### Ethics approval

The protocol of the study is approved by the Institutional Ethics Committee (IEC) of the participating sites (Ethics Committee for Human Studies, National Institute for Research in Reproductive and Child Health; Institutional Ethics Committee, St. John’s Research Institute; Ethics Review Committee, Society of Applied Studies; Institutional Ethics Committee, Kalinga Institute of Medical Sciences; Institutional Human Ethics Committee, All India Institute of Medical Sciences; Institutional Ethics Committee, National Institute of Nutrition). The study adheres to the principles specified in the Declaration of Helsinki [36]. The study is registered at www.ctri.nic.in (CTRI/2025/06/088025).

Prior to the enrollment, every participant will be provided with a participant information sheet in local language explaining the purpose of the study, its risks, benefits, role of the participants and other details. There will be no coercion of any kind to participate in the study. The participants will not be deprived of any services being offered to them if they decide not to participate in the study. Written informed consent will be obtained from all the participants. For adolescent boys and girls (between 12- < 18 years) written assent will be taken and written informed consent will be taken from the parents/legal guardian. For children, written informed consent will be taken from the parents/legal guardian. The privacy and confidentiality of the participants will be maintained during data collection. The data for the study will be stored in a password protected computer/laptop and only the study investigators and the team members will have access to this data. All the personal identifiers will be removed before publication of results and report submission.

### Comprehensive intervention package: evidence summary

The intervention package tested in the PRAKASH study is grounded in a comprehensive evidence synthesis exercise jointly undertaken by the ICMR, NITI Aayog, MoHFW and partner institutions. This exercise consolidated findings from national program data, research and expert consultations to identify interventions with the strongest potential to reduce anemia in the Indian context. The resulting package, incorporated under AMB 2.0, brings together six pillars: [1] Test–Treat–Track until resolution, [2] prophylactic iron and folic acid supplementation, ensuring high compliance[3] anemia-relevant health interventions, [4] fortified rice distribution through public systems, [5] dietary diversification and promotion of iron-rich foods, and [6] behavior change communication through Jan Andolan. A summary of evidence for the various interventions for anemia reduction has been presented in Table 2.

**Table 2 pone.0351414.t002:** Summary of the evidence for various interventions for anemia reduction.

Interventions within AMB	Age-Group	Summary evidence from systematic reviews–
1) Iron Folic Acid Supplementation (for Prophylaxis)	Children under 5 years	RR: 0.61(95% CI 0.50–0.74)^26^
	School-age Children (5–12 years)	RR: 0.50(95% CI 0.39–0.64)^27^
	Women of Reproductive Age	RR: 0.39 (95% CI 0.25–0.60)^28^
	Pregnancy	RR: 0.30 (95% CI 0.19–0.46)^29^
5) Deworming Interventions	Children	RR: 0.82(95% CI 0.60–1.11)^30^
	Pregnant Women	RR: 0.85 (95% CI 0.72–1.00)^31^
	Non-Pregnant Women	MD 3.02 g/L(95% CI 0.1–6.0 g/L)^32^
6) Delayed cord clamping	Early vs. delayed cord clamping in term infants	RR 2.65,(95% CI 1.04 to 6.73)^33^
7) Rice Fortification	General population	RR: 0.72 (95% CI 0.54–0.97)^34^
8) Dietary diversification	Pregnant women	AOR:2.15 (95% CI,1.66–2.65)^35^

RR: Relative Risk; MD: Mean difference; AOR: Adjusted Odds Ratio

These interventions will be implemented through existing health system platforms, Integrated Child Development Services (ICDS), and school health programs, with planning, implementation, and evaluation guided by the Implementation Research Logic Model [37]. Details pertaining to the logic models have been provided in S1 Table.

1. **Test–Treat-Track until resolution**: Systematic annual hemoglobin screening will be conducted for all beneficiaries across the six study sites. This screening will serve as the primary entry point for identifying individuals with anemia. Individuals diagnosed with anemia will receive appropriate treatment and be monitored until resolution. Mechanisms will be in place to track both nutritional and non-nutritional causes of anemia, such as sickle cell disease and thalassemia. The strategy will primarily focus on four high-burden groups children 6–59 months, adolescent girls, pregnant women, and women of reproductive age. Adolescents’ boys and younger children (5–9 years) will also be included in the strategy. Regular quarterly follow-ups by frontline workers will help ensure treatment compliance, early relapse detection, and sustained recovery.2. **Prophylactic iron and folic acid supplementation:** In parallel with screening, prophylactic IFA supplementation will be implemented to mitigate the risk of anemia across populations. ASHAs and Anganwadi workers will maintain updated beneficiary line lists and ensure the distribution of tablets or syrups in accordance with program guidelines. Counseling and follow-up will be emphasized to enhance adherence, address common barriers such as side effects, and ensure continuity of prophylaxis.3. **Anemia relevant health interventions:** To comprehensively address anemia, the intervention package will integrate maternal, child health, and infection-control practices. This includes promotion of delayed cord clamping at birth, iron supplementation for low-birth-weight infants, and routine deworming. Water, Sanitation, and Hygiene (WaSH) behaviors will be promoted as preventive measures. Additionally, individuals diagnosed with acute or chronic infections such as malaria, tuberculosis, HIV, or hepatitis will also undergo anemia screening and receive appropriate management, thus linking infectious disease control with anemia reduction.4. **Fortified rice through Public Distribution Systems:** Nutrient security will be strengthened by leveraging government-supported food distribution programs. Fortified rice is already being distributed through the Public Distribution System (PDS), Integrated Child Development Scheme (ICDS), and Pradhan Mantri Poshan Shakti Nirman (PM-POSHAN) (mid-day meals) but through the study there will be efforts to generate community awareness and sensitization campaigns to promote acceptance and regular consumption of fortified rice. Monitoring will be conducted using official distribution records and household surveys to assess uptake and effectiveness in addressing dietary iron gaps.5. **Dietary diversification and promotion of iron-rich foods:** Dietary modification is an essential pillar for long-term anemia prevention. The intervention will promote consumption of iron, folate, and vitamin B12-rich foods, including millets and other traditional staples. Beneficiaries will be counseled at Village Health and Nutrition Days, Ayushman Arogya Mandirs, Self-Help Groups, and Anganwadi Centres. Practical demonstrations such as recipe sessions and use of dietary diversity checklists will reinforce key messages. Schools will serve as a critical platform, incorporating nutrition education into the curriculum, training student health ambassadors, and organizing activities under the “Eat Right” campaign. Program menus under PM-POSHAN and ICDS will also be reviewed to align with micronutrient standards. Communication strategies will employ Information, Education, and Communication (IEC) materials, Short Message Service, social media, and Ayush Ahaar campaigns to reinforce consistent dietary practices.6. **Behaviour change communication through Jan Andolan:** Finally, community engagement through Jan Andolan will ensure sustainability and collective responsibility for anemia control. This approach will emphasize advocacy, capacity building, and partnerships with schools, self-help groups, and local organizations. Social mobilization efforts will highlight the importance of annual screening, adherence to IFA supplementation, acceptance of fortified foods, and inclusion of diverse diets in daily meals. By positioning anemia reduction as a community priority, the intervention aims to build momentum toward a sustained, population-level movement.

Together, these six strategies create a comprehensive and integrated package that combines biomedical, nutritional, and behavioral approaches. By placing annual anemia screening at the center, the PRAKASH study seeks to ensure early identification and continuous management, while reinforcing prevention through supplementation, food-based strategies, fortified staples, and community mobilization. This integrated package is expected to provide a scalable and sustainable model for anemia prevention and control.

A detailed overview of the delivery mechanism of the 6 intervention strategies has been provided in S2 Table.

### Conceptual framework

The PRAKASH study will be guided by the Consolidated Framework for Implementation Research (CFIR) and the Expert Recommendations for Implementing Change (ERIC). CFIR provides a structured lens to examine contextual determinants of implementation across five domains, while ERIC offers a menu of evidence-informed strategies to address identified barriers. Together, these frameworks will inform the design and delivery of the intervention package, guide model development, and define indicators for monitoring performance. A detailed list of the five domains along with the underlying constructs has been provided in Fig 1 [38]. Based on the initial formative research, stakeholder inputs, and field experience, a prototype set of strategies has been identified for the CFIR constructs and will be refined iteratively during implementation.

**Fig 1 pone.0351414.g001:**
[figure not shown]
CFIR framework highlighting the five domains along with the underlying constructs.

1. **Innovation (intervention) characteristics:** A central construct is adaptability, ensuring that the evidence-based AMB 2.0 interventions are responsive to local needs and preferences. Local needs assessments and community engagement will help tailor service delivery strategies. For example, if supplementary nutrition programs are perceived as poor quality or underutilized, discussions will be held with service providers, supervisors, and program managers to adapt delivery mechanisms.2. **Outer setting:** This domain reflects the wider policy, socio-economic, and cultural environment. Two key constructs are cosmopolitanism and patient needs and resources. Strategies include building coalitions with state and district health authorities to ensure alignment with existing programs, mobilizing communities through social and behavior change communication (SBCC), and increasing demand for anemia services. Awareness campaigns will use a mix of mass media (print, audiovisual, social media) and community-level platforms such as street theatre, school programs, and health fairs to reinforce the importance of anemia prevention and management.3. **Inner setting:** The organizational environment in which interventions will be delivered include health facilities, schools, and ICDS centers. Structural gaps will be addressed through strategies such as improving physical infrastructure, strengthening record systems for anemia testing and tracking, and decentralizing service delivery points where access barriers exist. Readiness for implementation will be enhanced through leadership engagement and technical support units comprising ICMR experts, state authorities, and local partners. These units will provide ongoing guidance, periodic review, and facilitate partnerships with academic institutions for training and capacity building. Hands-on training and supportive supervision for frontline workers will focus on practical counseling and problem-solving skills.4. **Characteristics of individuals:** Successful implementation will also depend on the motivation, knowledge, and capacity of individuals engaged in delivering or receiving interventions. These include beneficiaries (children, adolescents, women), community health workers, nurses, doctors, ICDS supervisors, school personnel, and local administrators. Tailored training, role clarification, and supportive supervision will strengthen individual commitment and capacity to deliver interventions effectively.5. **Implementation process:** This domain emphasizes stakeholder engagement, execution, reflection, and evaluation. Strategies include conducting educational meetings and outreach visits to build knowledge, developing an implementation blueprint with clear goals, milestones, and indicators, and preparing user-friendly educational and communication materials. Local consensus discussions will foster shared ownership, while champions and opinion leaders will be identified to advocate for anemia control. Iterative cycles of implementation will involve small tests of change, concurrent monitoring, and feedback to refine strategies. Tools for quality monitoring, periodic audits, and readiness assessments will ensure that barriers and facilitators are continuously identified and addressed.

By applying CFIR to identify determinants and ERIC to operationalize strategies, the PRAKASH study aims to create a dynamic, context-sensitive, and scalable model for implementing evidence-based interventions to reduce anemia.

